### Implementation {16c}

The study design adopts a non-randomized approach, with an initial period during which clusters 1-5 are not exposed to the intervention. At regular intervals referred to as “steps”, clusters transition from the control to the intervention, leading to a systematic exposure until all clusters undergo the RISEinFAMILY project: a study protocol for the integration of families at Neonatal Intensive Care Units (NICUs) to empower them as primary caregivers, 20-11-2023 14-02-2024 page 12 of 21 crossover. Towards the study's conclusion, a phase ensues where all clusters uniformly experience the intervention. Data collection persists throughout, allowing each cluster to contribute observations during both control and intervention periods.

## Assignment of interventions: blinding

### Who will be blinded {17a}

Given the logistical and regulatory challenges in implementing randomization at clinical sites 1 to 5, blinding is not feasible. This is due to variations in hospital size and the internal time required to address logistical and regulatory issues. The primary objective remains the achievement of an equitable distribution of patients between the control and intervention groups. Consequently, hospitals and healthcare professionals involved in this trial will not be blinded for the assigned trial protocol.

### Procedure for unblinding if needed {17b}

The design is open-label with only outcome assessors being blinded so unblinding will not occur.

## Data collection and management

### Plans for assessment and collection of outcomes {18a}

Data will be collected by researchers at participating hospitals and stored anonymously in a digital database (Research Electronic Data Capture; REDcap). Data will be stored in accordance with guidelines issued by the Spanish Data Protection Agency. Independent monitors will perform source data verification and assess the performance of trial procedures at least once a year at each site. FIBHULP will be responsible for the data management and storage of the study data. The veracity of the data will be ensured through the training of the professionals in charge of the REDCap database. In addition, a database user manual has been included in the study folder accessible to all researchers.

There will be several time points for data entry: screening, enrolment, weekly visit up to discharge to home or transfer to a non-FICare centre, short-term clinical outcome assessment, mid-term clinical outcome assessment and long-term clinical outcome assessment. If the infant in the meantime has been discharged to a step-down unit, data should be sought from the specific unit. If this is not possible, data should be used until the date of discharge to the step-down unit.

### Plans to promote participant retention and complete follow-up {18b}

Intermediate trial report is planned to confirm that clinical sites are aligned with the estimated recruitment rates, or to refine. This will facilitate reaching the calculated sample size.

### Data management {19}

FIBHULP will be responsible for the data management and storage of the study data (on a database) including:*Data storage and backup*: The study server running the database is regularly maintained by the manufacturer. Twice a day a backup of the database with pseudonymised study data and the application data is automatically generated. Further storage of the dump files in an additional secure area and protected by a password will be issued. These backups can be used to restore the data and the application for electronic data capture on another server within a short time period.*Data validation*: Data will be validated according to the data validation plan.*Data coding:* medical history, adverse events (when applicable please refer to the assessment of safety section of the protocol) and any abnormality obtained on any study test result will be coded using MedDRA and concomitant treatments using WHO-DD. The codification procedure is described in a specific manual.

After conducting all data validation and the final review, the study database will be considered as completed and its containing data as reliable. At this moment, the study database will be closed and transferred to the Biostatisticians team for data analyses.

At the end of the study, a copy of the site-specific records will be provided to each principal investigator.

### Confidentiality {27}

The study staff will ensure that the participant´s anonymity is maintained. The participants will be identified only by a participant code on the eCRF and any electronic database. All documents will be stored securely and only accessible by study staff and authorised personnel. Applicable regulations for storage, transmittal and disclosure of patient information will be followed at all times. The study will comply with the Data Protection Legislation in each country. Following formal admission to the study, patient data will be recorded in the hospital case record in the usual way including the circumstances of their entry to the study. Additionally, data will be held in case report forms (eCRF). These files will be identified by a study code, date of birth and participant code only. Representatives from the Sponsor and from the regulatory authorities will be given access to the records that relate to the study. They will have full access to the anonymous eCRFs for the purposes of data validation. Results of the study may be communicated at scientific meetings and will contribute to the scientific literature. At no time, will this be done in such a way that an individual patient may be identified.

### Plans for collection, laboratory evaluation and storage of biological specimens for genetic or molecular analysis in this trial/future use {33}

See above 26b; there will be no biological specimens collected.

## Statistical methods

### Statistical methods for primary and secondary outcomes {20a}

The primary analysis will be conducted in the intention-to-treat (ITT) population including all enrolled patient-family dyads who received at least one task training according to protocol procedures.

Descriptive statistics will be recorded for each group with mean, median and standard deviation for numerical variables and absolute and relative frequencies for categorical variables. 95% confidence intervals (CIs) will be provided. Comparisons between control and intervention groups will be performed using chi-square tests for categorical variables, analysis of variance for normally distributed continuous variables, and Mann–Whitney or Kruskal–Wallis tests for non-normally distributed continuous variables. Through a mixed-methods research approach and techniques both quantitative and qualitative, the following impacts will be evaluated: (a) effect of intervention: the control and the intervention group dataset from the non-FICare-experienced centres will be compared; (b) effect of “expertise” on outcomes: comparisons will be conducted between datasets from already trained FICare centres and those from the non-FICare-experienced centres.

Socio-economic sustainability: Health economics analysis based on the value of implementation framework will be conducted to assess the cost-effectiveness of RISEinFAMILY implementation strategies. The difference between the total net benefit of perfect adoption and the total net benefit of current implementation will generate the expected value of perfect implementation (positive values would characterise cost-effective implementation strategies). The analysis will also allow identifying differences in delivering RISEinFAMILY in different countries/health care settings.

Psychological assessment of experiences collected by either the NICUs staff and the families enrolled in the pilots will be conducted. Gender differences will be explored in relation to socioeconomic and cultural background.

For our primary hypothesis, we will compare infant standardised weight gain velocity between the two groups over the 4-week study period using generalised linear mixed modelling (GLMM). For our primary outcome, we will compare infant standardised weight gain between the two groups over the study period defined as the change in Patel’s growth pattern measured weekly from enrolment until day 28 post-enrolment, testing an interaction term between group and post-baseline weight measurements. We will adjust for additional covariates using a hybrid approach, forcing in known confounders of gestational age and study site and using backward stepwise selection to retain covariates that contributed *p* < 0.1 to the final model from potential confounders. Additionally, we will conduct sensitivity analyses by adding in weight measured at discharge.

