### Interventions

#### Explanation for the choice of comparators {6b}

A cohort of patients, born at clinical sites 1 to 5 from the beginning of the study to the time assigned to start the intervention, will be assigned to the control group, representing standard neonatal care.

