#### Intervention description {11a}

The study will start at the same time at all participating sites that will continue to provide routine clinical care according to their current policies. Prospective data gathering will be accomplished.

A start point for the experimental intervention (3, 6, 9, or 12 months from the start of the study) will be assigned for each clinical site (1 to 5) taking into account the expected time internally needed to overcome all logistics and regulatory issues with a potential impact on FICare implementation. A 3-month wash-out period will be used for the local training process and assessment of site readiness, while enrolment will be halted. After that, recruiting will continue, and the experimental intervention will be started. Clinical sites 6 and 7 will run the experimental intervention from the start of the study, without pauses.

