The family training process relays on three cornerstones: (a) individualised theoretical and practical learning by tasks through face-to-face sessions at the cot-side, following an individualised teaching plan adjusted to the baby’s clinical condition and the wish of the parents; (b) family workshops, held as presential, online or hybrid format, that intend to gather parents during 45-min open sessions on relevant topics about the learning contents, to express their doubts and concerns, as well as to share their experiences with other families; (c) registry of teaching activities and task certification once proficiency is fully accredited in a given task, and the family caregiver is allowed to do this task autonomously.

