#### Criteria for discontinuing or modifying allocated interventions {11b}

The criteria for discontinuing or modifying allocated interventions for a given trial participant include parents’ request for temporary suspension due to personal reasons or the patient’s worsening condition leading to their desire to withdraw from active participation.

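### The primary set called intention-to-treat requires a task training that control dyads cannot receive; if controls are exempted, the exclusion acts after enrolment and on one group only

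*Protocol article*

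**What the plan says.** All references are to the protocol article.

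- **Analysis set.** Statistical methods {20a} places the primary analysis in an intention-to-treat population, "including all enrolled patient-family dyads who received at least one task training according to protocol procedures". It gives no separate rule for controls.
- **Contrast.** The same section says that, for the effect of the intervention, "the control and the intervention group dataset from the non-FICare-experienced centres will be compared".
- **Controls.** Under Explanation for the choice of comparators {6b}, infants born at sites 1 to 5 before the site's assigned start "will be assigned to the control group, representing standard neonatal care". Intervention description {11a} says that sites at first "will continue to provide routine clinical care according to their current policies", and Implementation {16c} describes "an initial period during which clusters 1-5 are not exposed to the intervention".
- **Training.** Training and certification describes the family programme as resting on "individualised theoretical and practical learning by tasks through face-to-face sessions at the cot-side", together with workshops and task certification. Local preparation comes after the control phase: "A 3-month wash-out period will be used for the local training process and assessment of site readiness, while enrolment will be halted" ({11a}).
- **Stopping.** Criteria for discontinuing or modifying allocated interventions {11b} names parents' requests for a temporary pause, and the infant's "worsening condition leading to their desire to withdraw from active participation".

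**The concern.** An intention-to-treat set keeps every enrolled participant in the group to which they were assigned, whatever they then receive. This set is conditioned on receiving a component of the intervention, which raises two problems.

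First, the condition cannot be met in the control phase, so the set does not support the comparison it was defined for.

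Second, the natural repair of exempting controls leaves a filter on an event after enrolment, in one group only. Starting training is unlikely to be unrelated to prognosis. The article adapts the teaching plan to the infant's condition and the parents' wishes, and it links withdrawal from participation to deterioration. Infants who worsen before a first task, or whose parents disengage, would leave the intervention group while similar infants remain among the controls. Sites are neither randomised nor blinded, so this adds to an existing risk of selection. The multiple imputation in {20c} would not repair it, because these dyads lie outside the analysis set.

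**Working it through.** **1. The plan's own sample size.** Inputs from Sample size {14}: difference 1.9 g/kg/d, SD 2.5 g/kg/d, alpha 0.05 (two-sided assumed, since the article does not say), power 95%.

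n per group = 2 × (1.960 + 1.645)² × (2.5 / 1.9)² = 44.996, which rounds up to 45. The t-test version gives 45.98, so 46. The stated 46 per group is reproduced; a one-sided test gives 38 and does not match. The comparison therefore needs at least 46 controls.

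**2. Literal reading.** A dyad must be enrolled and have received at least one task training under the protocol's procedures.

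- Control dyads are enrolled before the site's start, under routine care and unexposed to the intervention ({6b}, {11a}, {16c}).
- Task training is the family arm of the intervention (Training and certification), and local preparation begins only in the wash-out ({11a}).
- So 0 of at least 46 control dyads can enter.

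The eligibility phrase in {10} about a caregiver being involved in the training does not change this, because no protocol training is delivered in the control phase. It carries the same ambiguity.

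**3. Condition applied to the intervention phase only.** Let u be the share of intervention dyads that never receive a task, and g the amount by which their infants grow less than those of trained dyads. With m the trained mean, the mean over all enrolled is (1 − u) × m + u × (m − g) = m − u × g. Dropping the untrained raises the intervention mean by u × g. The article gives neither u nor g; both ranges are assumptions.

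- u = 5%, g = 1.9: 0.05 × 1.9 = 0.095, about 0.1 g/kg/d.
- u = 20%, g = 3.0: 0.20 × 3.0 = 0.60 g/kg/d.

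**4. Separating dilution from selection.** If training delivers the planned 1.9 g/kg/d and untrained infants get none of it, then 1.9 of the gap is lost effect. Only g − 1.9 reflects worse prognosis.

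- g = 1.9: the selection part is 0.
- u = 20%, g = 3.0: the selection part is 0.20 × (3.0 − 1.9) = 0.22 g/kg/d, which is 0.22 / 1.9 = 12% of the target. The remaining 0.20 × 1.9 = 0.38 g/kg/d is dilution.

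**5. Price of keeping everyone.** With untrained dyads retained at zero effect, the difference becomes 1.9 × (1 − u). The figures below use the article's two-group formula (normal approximation, no clustering).

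| u (assumed) | Difference, g/kg/d | Power at 46 per group | n per group for 95% |
|---|---|---|---|
| 5% | 1.81 | 93% | 50 |
| 10% | 1.71 | 91% | 56 |
| 20% | 1.52 | 83% | 71 |

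**The case against.** The strongest reply is that nobody would run the literal version. The article defines a control cohort, sizes it and says it will be compared, so the condition can only have been meant where training exists. That is probably the intention, but no section states it, and it leads straight to the one-sided exclusion.

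Second, the never-trained group may be small. Eligibility {10} already excludes infants unlikely to survive or scheduled for early transfer, and asks parents to commit to at least seven days of involvement. Section {11b} does not say that withdrawal happens before a first task, and a family that stops after one task stays in the set. This stands as a limit on size. It does not remove the exclusion.

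Third, one could call this an ordinary modified intention-to-treat set. A received-treatment condition is even-handed only if both groups can meet it, and here one cannot.

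Fourth, the population could be left to the analysis plan. But the article does not omit it: it states one and gives it a label that does not fit.

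**Conclusion.** The definition is wrong as written and must be changed before analysis. Literally it leaves no controls. Under the charitable reading it is a modified intention-to-treat set with a one-sided exclusion after enrolment, which can favour the intervention in the infant and parent comparisons. The size of that bias cannot be derived from the article. Under the assumed ranges the total shift is about 0.1 to 0.6 g/kg/d, of which at most about 0.2 is selection beyond a lost effect of 1.9.

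Some stronger readings are tempting but not supported:

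- **The whole shift as selection bias.** A reader might present 5 to 32% of the 1.9 target (0.095 / 1.9 to 0.60 / 1.9) that way. Most of it is dilution, and the inputs are assumptions.
- **230 lost controls.** A reader might multiply 46 by five sites. This fits 552 = 12 × 46 (five sites with two phases, two with one), but the article states 46 per group, not per site.
- **Every primary and secondary outcome is affected.** Staff outcomes are not dyad data, and training completion and time to completion have no control counterpart.
- **An as-treated analysis.** Nobody is regrouped by treatment received; some are left out.

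**What to change.** 1. For the control-versus-intervention comparison in {20a}, define the primary set as all enrolled dyads at sites 1 to 5, analysed by the phase their site was in, regardless of training received.
2. State one rule for assigning phase and make it agree with {6b}, which classifies controls by when they were born. Say whether the birth or the enrolment date governs, and how infants are classed when the two fall on different sides of the site's switch.
3. Keep sites 6 and 7 for the expertise comparison, also with all enrolled dyads.
4. Use the set with at least one task training only as a supportive analysis, and do not call it intention-to-treat.
5. For the proportion of families completing training, use all enrolled intervention-phase dyads as the denominator. Dropping those who never start would inflate it.

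The cost is a short rewording of the protocol and the analysis plan. No new kind of data is needed: the weekly data entry in {18a} is not tied to training. The estimated effect may be somewhat smaller, and any loss of power depends on the untrained share.

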**Methods:**

RISEinFAMILY is a pluri-cultural, stepped wedge cluster controlled trial conducted in Spain, Netherlands, the UK, Romania, Turkey, and Zambia. Eligible participants include infant-family dyads admitted to the Neonatal Intensive Care Unit (NICU) requiring specialised neonatal care for a minimum expected duration of 7 days, provided there are no comprehension barriers. Notably, this study will incorporate a value of implementation analysis on FICare, which can inform policy decisions regarding investment in implementation activities, even in situations with diverse data.

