### Eligibility criteria {10}

We will include infants born with birth weight at or below 1500 g or gestational age at or below 34 weeks, any other peri-neonatal condition anticipating NICU specialised care with an admission for at least 7 days and the decision to provide full life support. Further, we will include parents if they are willing to spend at least 6 h per day at NICU or committed to attending educational sessions, an active involvement in care of their infant for at least a 7-day period, not to have an intellectual or language barriers to understanding, at least one primary caregiver is involved in the training and signed informed consent. We will exclude infants with the decision not to provide full life support, critical illness unlikely to survive or scheduled for early transfer to another non-FICare hospital. We will exclude parents if they have an intellectual handicap that makes learning-understanding difficult, communication cannot be established even with a translator, have mental psychiatric problems or under legal supervision, or guardianship of social services, and finally, lack of parental signed informed consent.

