### Outcomes {12}

The study’s primary outcomes are as follows: (a) RISEinFAMILY implementation: proportion of families completing basic and advanced training levels (observed vs expected), average time to complete basic and advanced training levels (observed vs expected) and average time of kangaroo care per day (hours); (b) short-term health infant’s outcomes: proportion of high-risk infants achieving and maintaining adequate growth patterns during NICU admission, defined according to Patel’s method [10, 11].

The study’s secondary outcomes are as follows: reported adverse event rate per 1000 patients/day, feeding patterns and major morbidities at 36 weeks postmenstrual age (PMA) or discharge, nosocomial infection [12], necrotising enterocolitis (Bell’s > stage 2), moderate-severe brain injury (worst cranial ultrasound) [13], parental needs, empowerment and psychological health (stress [14], anxiety and depression [15, 16], self-efficacy [17], bonding [18], resilience [19]), professional’s self-care and satisfaction (anxiety and depression [15], burnout [20], post-traumatic stress [21], work and well-being [20]).

The study’s exploratory outcomes are as follows: economic impact (level of post-implementation utilisation of FICare, resources and costs associated with FICare implementation, cost-effectiveness estimates compared to the current care, expected value of current implementation and expected value of perfect implementation); mid-term infant’s general health (growth pattern during the first 12 months from birth, use of health system facilities after discharge); long-term neurodevelopment (survival without neurodevelopmental disabilities).

Specific items and test batteries are stated in Additional file 1.

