### Sample size {14}

No previous study has assessed the effect of FICare intervention on growth velocity expressed in g/kg per day. Therefore, for sample size calculation in the RISEinFAMILY project, we will follow one of the most recent studies evaluating the effect of individualised breast milk fortification on weight gain expressed in the same units [34]. In this study, based on their own data obtained in a pilot and other literature data, the authors assumed 1.8 ± 3.1 g/kg/d as a reasonable and clinically meaningful difference in weight gain. With a total *N* of 103 (experimental group *N* = 52, control group *N* = 51), they found a difference in the weight gain of 1.9 g/kg/d and a standard deviation of 2.5 g/kg/d.

Using this information, we calculated the minimum size for the intervention (FICare) and the control (standard care) group in the RISEinFAMILY study. Our null hypothesis is no impact of FICare and, as a consequence, the mean of the weight gain in both the intervention and control groups will be the same. Our alternative hypothesis is a difference in the mean weight gain between FICare and the control group of at least 1.9 g/kg/d [34]. We impose a type I error (probability of rejecting the null hypothesis when it is true) of 5% (*α* = 0.05), and a type II error (probability of not rejecting the null hypothesis when it is false) also of 5% (> 0.05), which provides a statistical power of 95%. The minimum sample size for intervention and control groups is given by at least 46 children in the intervention (FICare) and other 46 children in the control (standard care) group.

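### If siblings are enrolled as separate infant-family dyads, the independent-sample tests named for group comparisons give standard errors that are too small; the plan should say how multiples form dyads and use a method that carries the pairing

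*Protocol article*

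**What the plan says.** The abstract (Methods) describes participants as infant-family dyads. The section Statistical methods for primary and secondary outcomes {20a} defines the primary analysis population as "all enrolled patient-family dyads who received at least one task training".

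Other sections count other units. Trial design {8} plans at least 552 babies. Sample size {14} asks for 46 children per group. Outcomes {12} states one primary implementation outcome as the "proportion of families completing basic and advanced training levels", observed against expected. These counts agree only if each family has one enrolled infant.

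Eligibility criteria {10} admit "infants born with birth weight at or below 1500 g or gestational age at or below 34 weeks", and also other conditions with an expected stay of at least 7 days. The article does not mention twins, siblings or multiple births, and it sets no limit on infants per family.

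For the group comparisons, {20a} states: "Comparisons between control and intervention groups will be performed using chi-square tests for categorical variables, analysis of variance for normally distributed continuous variables", with Mann-Whitney or Kruskal-Wallis tests for non-normal variables. The primary weight-gain hypothesis has its own method, a generalised linear mixed model on weekly weights, "forcing in known confounders of gestational age and study site". The random effects of that model are not listed. Adjustment for clustering is named only for imputation and the missing-data sensitivity analyses ({20c}), without saying at which level.

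**The concern.** A population selected for preterm birth and low birth weight can be expected to contain multiples. Under Explanation for the choice of comparators {6b} and Intervention description {11a}, an infant's group follows from the site and the calendar period. Siblings admitted together therefore share a group. Their outcomes are likely to be positively correlated, and in that case the variance of a group mean exceeds what an independent-sample test assumes.

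Two kinds of outcome are exposed. The first is infant secondary outcomes such as feeding pattern, infection and other morbidities, if each sibling is a separate record. The second is the parental scales (stress, anxiety, depression, self-efficacy, bonding, resilience), if a parent's score is held under each infant. In that case the same number appears twice, and families with multiples get extra weight. Superiority on parental mental health is a stated aim in Objectives {7}, so nominal error rates and intervals for these scales matter. No mixed model is named for them.

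**Working it through.** **1. The plan's own figure.** Inputs from Sample size {14}: difference 1.9 g/kg/d, SD 2.5 g/kg/d, alpha 0.05 (taken as two-sided), power 95%.

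- n per group = 2 × (1.960 + 1.645)² × (2.5/1.9)² = 2 × 12.995 × 1.731 = 45.0.
- The t-test version gives 45.98, so 46.

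The stated 46 is reproduced. It is a calculation for independent infants, with no allowance for families (or sites).

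**2. Design effect for twin pairs.** Let a share f of the n infants in a group belong to twin pairs, both in that group, with within-pair correlation ρ. There are fn/2 pairs, so

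- variance of the sum = nσ² + 2 × (fn/2) × ρσ² = nσ²(1 + fρ), and DE = 1 + fρ;
- true SE / naive SE = √DE;
- true two-sided error of a nominal 5% test = 2(1 − Φ(1.96/√DE)).

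**3. Assumed inputs.** The documents give neither f nor ρ. The main range is f = 0.2 to 0.3. ρ = 0.5 stands for an infant outcome, and ρ = 1 for one parent's score entered under both twins.

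| f | ρ | DE | √DE | 1.96/√DE | True error |
|---|---|---|---|---|---|
| 0.2 | 0.5 | 1.10 | 1.049 | 1.869 | 6.2% |
| 0.3 | 0.5 | 1.15 | 1.072 | 1.828 | 6.8% |
| 0.2 | 1.0 | 1.20 | 1.095 | 1.789 | 7.4% |
| 0.3 | 1.0 | 1.30 | 1.140 | 1.719 | 8.6% |

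Over a wider range (f 0.1 to 0.4, ρ 0.3 to 1.0), DE runs from 1.03 to 1.40. The true SE is 1.5% to 18% larger than the naive one, and the true error is 5.4% to 9.8%.

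**4. Check by simulation.** Naive t-tests with 46 infants per group and no true difference, 20,000 replicates, rejected in 5.2% of runs without twins. They rejected in 6.8% at f = 0.3, ρ = 0.5 and in 8.7% at f = 0.3, ρ = 1. The formula is confirmed.

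**5. Power.** At f = 0.3, ρ = 0.5, the 46 per group would become 46 × 1.15 = 52.9, so 53; power at 46 would be 92.5%. The trial plans 552 babies, or 276 per group if split equally (an assumption). Even at DE = 1.40 the effective number is 276/1.40 = 197 per group, and power for 1.9 g/kg/d stays above 99.9% if pairing is the only dependence. The harm is to intervals and error rates, not to power.

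**The case against.** The strongest reply is that the article never says a twin pair makes two dyads. The sentence on the analysis population defines who is included, not how many records a family contributes. Three stronger readings are tempting, and the documents do not support them.

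- A reader might infer that a parent's questionnaire is in fact counted twice. No section says so. Table 1 places parental questionnaires in the same participant schedule as infant weight, which leaves duplication possible but does not show it.
- A reader might infer that the training-completion proportion has too many false positives. It is worded per family and as observed against expected, and no control-versus-intervention test of it is named. Its wording already points to one record per family.
- A reader might infer that the primary growth analysis treats siblings as unrelated. It is a mixed model with unlisted random effects. The article names no family level, but the model can hold one, and the full protocol or analysis plan may specify it.

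The case forms are not shown either. Confidentiality {27} lists a study code, date of birth and participant code as file identifiers, but this does not prove that siblings cannot be linked. The magnitude rests wholly on an assumed twin share and correlation, and eligibility is not confined to preterm infants.

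Much of this reply stands, and it makes the point conditional. It does not remove the point, because the article does more than leave a detail open. It names tests for the group comparisons that cannot carry sibling pairing, and it applies them to a population that may contain siblings.

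**Conclusion.** The point holds in conditional form. The dyad is not defined for multiple births, and the tests named in {20a} for group comparisons assume independence. If siblings enter as separate dyads, standard errors will be too small for infant secondary outcomes. The same holds for parental scales if scores are stored per infant.

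With 20-30% of infants in twin pairs, the understatement is modest for infant outcomes at a correlation of 0.5: the true SE is about 5-7% larger and a 5% test runs at about 6.2-6.8%. It is larger for duplicated parent scores: the true SE is about 10-14% larger and the test runs at about 7.4-8.6%. These sizes depend on assumptions that the documents can neither confirm nor refute; the direction does not, provided siblings correlate positively. Dependence within sites is a separate matter and comes on top. This should be corrected, but it does not threaten the trial's power.

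**What to change.** - State how twins and higher multiples form dyads, and whether one or all siblings are enrolled.
- Analyse parental scales with one record per parent per time point. Analyse training completion and time to completion with one record per family, as Outcomes {12} already words completion.
- For infant outcomes, replace the independent-sample tests with a model that has a family random intercept within site, or use standard errors clustered on family. Where most families have one infant and the outcome is binary, the random intercept may be hard to estimate, and clustered standard errors are then the practical choice. Name the family level in the growth model too.
- Make sure siblings are linked in the database. Trial status reports enrolment from February 2023, so any missing link should be back-filled before the database is closed.

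The cost is one linking variable if none exists, a few sentences in the analysis plan, and slightly wider intervals. No extra recruitment is needed on this account.
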